**Fig. 3 Fig3:**
[figure not shown]
Power as a function of the odds ratio for the effect of low cost or navigator intervention at several levels of the effect of the second intervention

These power calculations do not account for a feature of our design which will improve the efficiency of the estimation further, and that is the inclusion of a baseline measures that predict invitation and testing of family member as described above. The inclusion of such measures can substantially improve the efficiency of estimation of the intervention effect in any design. For cluster randomized trials such as this one, the effect of the baseline cluster level covariate on improving power increases as the ICC increases. Thus, at smaller ICCs than we assumed in our calculations above, our power will be substantially higher than shown. But if it is as high as assumed then the benefits from inclusion of the baseline covariate will be even larger [17].

The estimates will be more precise, and the power will be higher for secondary aim 1 (family invite fraction) as the proportion of relatives invited will be higher than those who get tested with the same denominator, as well as for the continuous outcome of secondary aim 2 (patient assessment of family communication) than for either of the binary outcomes.

### Descriptive aims

Unlike many randomized trials where a sample recruited at academic or other medical centers is not very generalizable, our sample is drawn with probability sampling from the entire population of patients tested for pathogenic variants in two large, diverse states. We have an opportunity to measure and describe a number of characteristics of the patient inception cohort using the SEER-based Georgia California Genetic Testing Linkage Initiative database which will be useful to examine the uptake of the intervention across different clinical and socioeconomic status (SES) subgroups (e.g., SEER Medicaid vs. other insurance, SEER census tract level SES, patient report of education level) and inform generalizability of our findings and the scaling of next-generation strategies.

## Discussion

The GIFT study is the first population-based randomized clinical trial to evaluate a direct-to-family, virtual, personalized, family-centered communication and decision-making tool. We have been highly successful at implementing all aspects of the study protocol as submitted at the time of initiation of the study including participant selection and enrollment procedures, the implementation of the intervention, and the collection of all pre-specified outcome measures. Our initial estimates of GIFT trial patient and relative participation documented in ClinicalTrials.gov prior to launch of the study were conservatively large, to ensure adequate power to detect even small differences across study arms, including potential interactions (see Table 3 above). Our revised estimates of GIFT trial enrollment described in the last amendment to clinicaltrials.gov prior to completion of the trial enrollment period (see Table 2 above) are sufficient to detect clinically meaningful difference across study arms. Lower than expected projections are due to several factors along the trajectory from patient selection through participant study flow. First, we sampled a lower number of patients than projected, largely due to overestimating the number of patients who were still alive at the time of selection (given a 2018–2019 diagnosis cohort) and some limitations on the project budget. Second, response rates to the baseline cohort survey were lower than expected, which has been a national trend in survey research during our study period largely due to barriers related to the peri-COVID-19 environment. Third, we overestimated the proportion of respondent patients who were eligible for the trial (who recalled a PV result on germline genetic testing). Fourth, we overestimated the expected proportion of eligible patients who would enroll in the GIFT trial (30% vs. 20%). The lower estimate appears to reflect patient uncertainty about the interest of family members in getting genetic testing, even though patients reported that very few relatives were tested at the time of completing their baseline survey. Finally, we also observed a lower-than-expected number of relatives invited by enrolled patients. Many enrolled patients reported feeling obligated to reach out to relatives before inviting them to GIFT, which influenced trial uptake in families. Enrolled patients’ uncertainty about providing relatives’ contact information was reduced over time through our persistent efforts to focus messaging on the value of the study for families, the quality of the team, and assurances of the protection of privacy. Invitation and enrollment of relatives is ongoing.

In summary, we view our experiences in this first large virtual intervention to deliver cascade cancer genetic risk education and testing in the community as a “glass half full”. Preliminary findings have shown that enrollees viewed their experiences favorably, but we did not achieve the participation we expected. The challenges we encountered are those that patients, families, and their clinicians face in practice every day. We have pinpointed the barriers to more robust uptake of the intervention, which will inform our next-generation intervention research: these include patients’ sense of the burden of obligation to contact relatives before being invited to our trial; patient reticence to re-visit prior informal and often clinically unsupported conversations with relatives; and the perception that the intervention has overemphasized an obligation to test vs. to deliver more effective cancer genetic risk education to relatives, so as to facilitate their shared decision-making about getting tested. However, as described in detail above, GIFT is sufficiently powered to detect clinically important differences across the study arms for the pre-specified primary and secondary outcomes. Our intervention experiences and outcomes inform strategies and tools to close the persistent gap in cascade genetic risk evaluation in families with hereditary cancer syndromes.

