**Relatives**	
Relatives invited to the GIFT Study	1,236 (3.3 relatives per enrolled patient)
Relative GIFT Study Participants	371 (expected enrollment rate = 30%)

**Table 3 Tab3:** Sample size summary estimates prior to launch of the trial

Study phase	Sample Size

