### Analysis plan

The analysis plan remains unchanged at the end of enrollment from that described in our IRB filing of 10/28/22 at the start of enrollment (see Study Protocol in Supplemental Material). As described above, we are testing the main effects of two interventions, represented by the separate platform design features of reduced vs. free test cost and web-based vs. human navigator communication and decision support. The 2 × 2 factorial design with block randomization at the level of the index patient (j) results in four groups of index patients of equal size. There are several analytic issues common to the primary and two secondary aims.

First, we do not hypothesize that there will be any synergistic effect of the two treatments on the log odds scale and thus assume that the effects will be additive. Conceptually we cannot think of any reason that the effect of the cost of the testing and any help provided by a navigator over the website have an obvious reason to be dependent on the level of the other. Thus, our primary outcome for the primary and secondary aims is the treatment effect of each intervention in a regression model without an interaction term.

The second analytic issue is that of informative cluster size. An assumption of the generalized linear multilevel models used in our analysis is that cluster size is not informative. The literature on family communication does not generally talk about family size as one of the factors that predicts health communication but there is little data one way or the other looking specifically at genetic testing. Thus, there is little to guide us on whether larger families are more or less likely to communicate well, or be likely to invite relatives, or whether relatives in larger families are more or less likely to get genetic testing when there is a potential health benefit. Thus, given the conditional independence assumption we will condition the models on cluster size with a threshold of including this covariate as a p value of 0.10 or less.

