### Sample size calculations

The number of enrolled subjects as achieved just prior to the close of enrollment was substantially lower than anticipated, however given considerable uncertainty in the planning stages about how successful our recruitment would be and the heterogeneity in the sample size requirements for the different aims, we had managed to design the trial such that the sample size for most of our aims were far larger than was needed to achieve a power of 0.8 with a alpha of 0.05.

Below we describe the calculations for power under the original and realized recruitment numbers.

For the primary aim we have two estimates, one for each of the two interventions in the factorial design.

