### Assumptions

Effect sizes for the intervention were proposed to be the minimum clinically significant and achievable effect for assumed testing rates varying by trial features as shown in Table 5.

**Table 5 Tab5:** Minimally detectable absolute difference between study arms

	No Navigator	Navigator
$50	10%	15%
Free	13%	18%

These probabilities reflect odds ratios of 1.4–1.5. To account for clustering in the relatives’ outcomes at the patient level, we assumed an estimate of 0.15 for the residual intra-class correlation (after accounting for the intervention effects).

We originally hoped to enroll 880 index cancer patients with a median of 8 eligible relatives. As described in our original protocol, with these assumptions, a simulation based on our planned analytic approach confirmed a power of at least 0.80 for the effect of zero cost of the genetic test and navigation support for any effect including or above these specified effect sizes. However, we had built in a substantial buffer against our assumptions being different from what we proposed, including our enrollment numbers and the power was considerably higher than 0.80 for the larger sample size as seen in the graphs below and at an odds ratio of 1.5 we still have a power of 0.80 for the realized enrolled population of 400 or higher (Fig. 3).

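### The Discussion claims sufficient power for the secondary outcomes, but no power is described for Secondary Aim 3, which rests on about 371 enrolled relatives

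*Protocol article*

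**What the plan says.** The article lists three secondary aims, in the aims section and again in Table 4. Aim 3 asks whether enrolled relatives complete formal genetic risk evaluation. It is measured by one question on the relatives' six-month survey.

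The Analysis plan says "There are several analytic issues common to the primary and two secondary aims" and then gives models for the primary aim and Secondary Aims 1 and 2.

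Under Sample size calculations the adequacy claim is limited: "the sample size for most of our aims were far larger than was needed to achieve a power of 0.8", with alpha 0.05. The only figure for the reduced enrolment concerns the primary aim: "at an odds ratio of 1.5 we still have a power of 0.80 for the realized enrolled population of 400 or higher". The text below Figure 3 adds, without figures, that power is higher for Secondary Aim 1 (same denominator, higher proportion) and Secondary Aim 2 (continuous outcome). Secondary Aim 3 is not mentioned.

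The closing paragraph of the Discussion then states, referring back to the detail above, that "GIFT is sufficiently powered to detect clinically important differences across the study arms for the pre-specified primary and secondary outcomes". Earlier in the Discussion, the pre-launch enrolment estimates are described as "conservatively large, to ensure adequate power to detect even small differences across study arms, including potential interactions".

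**The concern.** The closing sentence is a positive claim that points to a description elsewhere in the article, and for Aim 3 no such description exists. It also drops the limit to most of the aims that the sample size section had set.

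The arguments given for the other two secondary aims do not carry over. Aim 1 shares the primary aim's denominator of all eligible relatives, about 412 × 8 = 3,296. Aim 2 is a continuous outcome on the 412 patients. Aim 3 is binary and is counted in enrolled relatives who answer a survey, of whom at most 371 are expected.

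If the claim stands, a non-significant Aim 3 result could be read, on the article's own authority, as evidence that navigation or free testing does not affect formal genetic risk evaluation. The data might be compatible with differences of ten points or more.

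**Working it through.** **1. The article's own figure.** Inputs: 400 families, 8 relatives each, intra-class correlation 0.15 (Assumptions), equal allocation (Analysis plan), two-sided alpha 0.05 (sidedness assumed).
- Design effect = 1 + (8 − 1) × 0.15 = 2.05.
- Effective relatives per factor level = 200 × 8 / 2.05 = 780.
- Averaging Table 5 over cost, the navigator contrast is 11.5% against 16.5%, a pooled odds ratio of about 1.52.
- SE = √[(0.115 × 0.885 + 0.165 × 0.835)/780] = 0.0175.
- Power = Φ(0.05/0.0175 − 1.96) = 0.81.

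The stated 0.80 at an odds ratio of 1.5 is reproduced for this setting.

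**2. Secondary Aim 3.** Table 2 expects 371 enrolled relatives, so 371/2 = 185.5 per factor level. The article gives no control rate, target difference, survey response or clustering for this aim. The control rates, response and design effects below are assumptions. The first case, full response and no clustering, is the most favourable.

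Power = Φ(|p₂ − p₁|/SE − 1.96), with SE = √[(p₁(1 − p₁) + p₂(1 − p₂))/n].

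| Control rate | Rate at odds ratio 1.5 | Power at odds ratio 1.5 | Difference detectable at 80% power | As odds ratio |
|---|---|---|---|---|
| 10% | 14.3% | 0.24 | 10.3 points | 2.3 |
| 20% | 27.3% | 0.38 | 12.7 points | 1.9 |
| 30% | 39.1% | 0.46 | 13.9 points | 1.8 |
| 40% | 50.0% | 0.49 | 14.4 points | 1.8 |
| 50% | 60.0% | 0.49 | 14.3 points | 1.8 |

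Less favourable cases:
- 70% response (n = 371 × 0.7/2 = 130 per level): detectable difference about 13 to 17 points; power at odds ratio 1.5 is 0.18 to 0.37.
- 70% response and a design effect of 1.2 (effective n = 108): detectable difference about 14 to 19 points.

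**3. Interaction at the original size (lesser point).** Inputs: 880 families, 220 per cell, 8 relatives each, Table 5 rates of 10%, 13%, 15% and 18%.
- Variance of the log ratio of odds ratios = design effect/(220 × 8) × Σ 1/[p(1 − p)], and the sum over the four cells is 11.11 + 8.84 + 7.84 + 6.78 = 34.57.
- Intra-class correlation 0.15 on the proportion scale: variance = 2.05 × 34.57/1,760 = 0.0403, SE = 0.20. Detectable ratio at 80% power = exp(2.80 × 0.2007) = 1.75.
- If 0.15 is read on the latent scale, about 0.07 on the proportion scale: design effect 1.49, SE = 0.17, detectable ratio 1.61.
- Power for a ratio of 1.3 is 0.26 to 0.33.

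The Table 5 main-effect odds ratios run from 1.24 to 1.59, so the smallest detectable interaction was larger than any of them.

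**The case against.** Four objections deserve weight.

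First, an article may leave detail to the full protocol, and this one refers to its supplement for the analysis plan and to an appendix for the Aim 3 question. That stands: the absence of an Aim 3 model or calculation is not itself the point. The point is that the Discussion asserts power and cites the article's own text as the source.

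Second, a reader might infer that the trial is shown to be underpowered for Aim 3. The documents do not support that. They give no control rate, response rate or clustering for this aim and do not define a clinically important difference. The odds ratio of 1.5 is the benchmark for a different outcome in a different population. Odds ratios of about 1.8 to 2.3 would be detectable in the favourable case, and covariate adjustment might help by an unstated amount. The claim is unsupported, not disproved.

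Third, a reader might take the reference to two secondary aims in the Analysis plan as a miscount. It can equally mean that the listed issues apply to the two secondary aims modelled there. Writing three would extend that text to an aim for which the article gives no model.

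Fourth, the interaction remark concerns a superseded enrolment target. The article hypothesizes no interaction, and no planned analysis depends on one. That makes it a minor wording matter. Only the suggestion that even small interactions were covered is overstated.

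**Conclusion.** The point holds in limited form. The Discussion's power claim reaches further than the power text, which covers the primary aim and Secondary Aims 1 and 2, and further than the sample size section's own wording. For Aim 3, power at an odds ratio of 1.5 stays below 0.50 at every control rate from 10% to 50%, even with full response and no clustering. The detectable difference is about 10 to 14 points in that case and about 14 to 19 points with 70% response and a design effect of 1.2. These figures are illustrations on assumed inputs. Nothing here questions the power for Secondary Aims 1 and 2. The interaction phrase is a secondary matter: at 880 families only a ratio of odds ratios of about 1.6 to 1.75 was detectable.

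**What to change.** - Limit the closing Discussion sentence to the outcomes for which power was described, in line with the sample size section.
- State the approximate detectable difference for Secondary Aim 3 at 371 enrolled relatives, with its assumptions (about 10 to 14 points before non-response and clustering), and describe Aim 3 as estimation-focused, reported with confidence intervals.
- Delete the reference to potential interactions in the Discussion, or qualify it with the detectable ratio of about 1.6 to 1.75 at 880 families.
- Leave the reference to two secondary aims in the Analysis plan as it is, unless a model for Aim 3 is added.

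The cost is a change of wording. No participants, data or analyses are added, but the stated power becomes less favourable.

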## Data Availability

No datasets were generated or analysed during the current study.

## Abbreviations

ARR: At-Risk Relatives
CHCR: Center for Health Communications Research
DSMC: Data and Safety Monitoring Committee
FGHP: Family Genetic Health Program
GCP: Good Clinical Practice Guidelines
GIFT: Genetic Information and Family Testing
GRE: Genetic Risk Evaluation
HBOC: Hereditary Breast and Ovarian Cancer
HCS: Hereditary Cancer Syndrome
HIPAA: Health Insurance Portability and Accountability Act
IMS: Information Management Services, Inc
IRB: Institutional Review Board
MGP: Multigene Panel
NCI: National Cancer Institute
PIC: Patient Inception Cohort
PV: Pathogenic Variant
QARC: Quality Assurance Review Committee
RCT: Randomized Control Trial
SEER: Surveillance, Epidemiology, and End Results
SES: Socioeconomic Status
SSL: Secure Socket Layer
UM: University of Michigan
US: United States
